## Abstract

**Background:**

Sudden loss of smell and/or taste has been suggested to be an early marker of COVID-19 infection, with most findings based on self-reporting of sensory changes at a single time point.

**Objective:**

To understand the onset, severity, and recovery of sensory changes associated with COVID-19 infection, this study will longitudinally track changes in chemosensory acuity among people with suspected COVID-19 infection using standardized test stimuli that are self-administered over 28 days.

**Methods:**

In a prospective, case-controlled observational study, volunteers will be recruited when they present for COVID-19 screening by respiratory tract polymerase chain reaction test (“swab test”). The volunteers will initially complete a series of questionnaires to record their recent changes in smell and taste ability, followed by a brief standardized smell and taste test. Participants will receive a home-use smell and taste test kit to prospectively complete daily self-assessments of their smell and taste acuity at their place of residence for up to 4 weeks, with all data submitted for collection through web-based software.

**Results:**

This study has been approved by the Domain Specific Review Board of the National Healthcare Group, Singapore, and is funded by the Biomedical Research Council Singapore COVID-19 Research Fund. Recruitment began on July 23, 2020, and will continue through to March 31, 2021. As of October 2, 2020, 69 participants had been recruited.

**Conclusions:**

To our knowledge, this study will be the first to collect longitudinal data on changes to smell and taste sensitivity related to clinically diagnosed COVID-19 infection, confirmed by PCR swab test, in a population-based cohort. The findings will provide temporal insights on the onset, severity, and recovery of sensory changes with COVID-19 infection, the consistency of symptoms, and the frequency of full smell recovery among patients with COVID-19. This self-administered and cost-effective approach has many advantages over self-report questionnaire–based methods and provides a more objective measure of smell and taste changes associated with COVID-19 infection; this will encourage otherwise asymptomatic individuals who are potential spreaders of the virus to self-isolate and seek formal medical diagnosis if they experience a sudden change in sensory acuity. This broadened case finding can potentially help control the COVID-19 pandemic and reduce the emergence of clusters of infections.

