## Introduction

Early identification of symptoms associated with SARS-CoV-2, which causes COVID-19, has been recommended to encourage early diagnostic testing and self-isolation and to reduce the risk of community spread of infection. High temperature, continuous dry cough, and fatigue are common clinical symptoms associated with COVID-19 infection; however, numerous recent reports from patients and clinicians worldwide have consistently identified a sudden loss of smell (anosmia) and/or taste (ageusia) as a key early symptom of infection [1-6].

Recent self-report questionnaire data from many countries highlights an association between sudden onset smell and taste loss and COVID-19 infection, with reported incidences of changes in sensory acuity ranging from 11% to >60% [7-13]. A recent systematic review and meta-analysis of studies investigating loss of smell and/or taste with COVID-19 infection reported a pooled prevalence of 52.7% and 43.9% for olfactory and gustatory dysfunction, respectively [14]. Also, Hopkins et al [15] found that 1 in 6 patients reported new onset anosmia as an isolated symptom. The onset of smell and/or taste loss is often abrupt and, unlike other upper respiratory tract infections, it often occurs in the absence of nasal obstruction [13,16]. Importantly, the loss of smell and/or taste occurs early during COVID-19 infection, often before the onset of more established symptoms [8,17-20], and this loss may be an important marker of infection. This finding has prompted many global public health bodies to recommend that individuals who experience sudden changes in sensory acuity should self-isolate and present for diagnostic testing [2-4,21-24].

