The COVOSMIA-19 study will standardize the smell and taste stimuli used by all participants to ensure consistency and provide a disposable, rapid, self-administered home use test, the Singapore Smell and Taste Test (SSTT), to minimize the risk of cross-contamination and infection spread. The trial will enable self-testing for up to 28 consecutive days and will provide a standardized longitudinal assessment of smell and taste function to enable tracking of the onset, severity, and recovery of the sensory changes reported to occur with COVID-19 infection. The standardized smell and taste test will also be compared with self-reported questionnaire measures of smell and taste changes and measured changes to sensory acuity using common household items (an approach previously used by [32]).

The primary objectives of this study are to (1) assess the prevalence of sudden changes in smell and taste sensitivity with COVID-19 infection in a population at risk for COVID-19 infection in Singapore, (2) establish the temporal onset, severity, and recovery of changes in smell and taste sensitivity with COVID-19 infection, and (3) evaluate the efficacy of the SSTT as a rapid, cost-effective, self-administered measure of changes to smell and taste compared to previous measures using household items. The secondary objective of this study is to investigate the effects of loss of smell and taste acuity on food enjoyment and appetite as well as to establish the impact of COVID-19 infection on food-related markers of quality of life. We hypothesize that loss of smell and taste acuity will be associated with COVID-19 infection, will return upon recovery from infection for the majority of patients, and will result in short-term reductions in appetite, food enjoyment, and food-related quality of life.

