## Methods

### Study Design

The study will track changes in smell and taste with COVID-19 infection using a prospective longitudinal, case-control study design. Participants will be recruited from volunteers presenting at hospitals and hospital facilities across Singapore for COVID-19 screening. After providing informed consent, the study participants will be asked to report on changes in their smell and taste sensitivity in the previous 2 weeks via a series of questionnaires; they will also be asked to prospectively track daily changes in smell and taste acuity using a self-assessment test and a series of questionnaire measures to measure the onset, severity, and recovery of changes in their chemosensory acuity for the next 28 days. A schematic of the study procedure is shown in Figure 1, and the schedule for enrolment and assessment is shown in Table 1.

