### Recruitment Procedure

Participants will be recruited from patients applying to a hospital and its ancillary units for COVID-19 screening by nasal swab polymerase chain rection (PCR) testing. Following their COVID-19 screening, individuals will be approached and invited to participate in this study and to provide informed consent.

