### Statistical Analysis

Using a case-control study design for people testing positive (case) or negative (control) for COVID-19 infection, data will be collected on changes in smell and taste loss that have occurred in the 2 weeks prior to the COVID-19 test and on smell and taste acuity changes measured on a daily basis for up to 28 days following the COVID-19 test. The data will be used for descriptive comparisons of the onset, duration, and severity of smell and taste changes with COVID-19 infection and to report on the incidence of these changes among participants testing positive for COVID-19 infection (and those recovering from infection).

Logistic regression analysis will be used to estimate the odds ratio for loss of smell and taste sensitivity as a predictor of testing positive for COVID-19 infection. This will also enable comparison of smell and taste loss as a predictor of COVID-19 infection compared to other symptoms, such as fever and dry cough. Pearson correlations will be used to investigate relationships between smell and taste changes and other symptoms. Time-series analysis of variance (ANOVA) models will be run to investigate temporal changes in smell and taste ratings over time, with baseline ratings in smell and taste acuity corrected for at an individual level. Linear mixed models will be used to test for significant differences in smell and taste acuity between groups, with participants stratified by their COVID-19 infection status.

Factor analyses, using oblique rotation and baseline home-use test responses (conducted in-clinic), will be conducted to assess the internal consistency of our smell and taste test. Adjusted odds ratios will be calculated to investigate the best predictors of recovery of smell and taste acuity postinfection. Linear regression will be run to examine whether responses to the smell and taste test predict responses to the household item odor test (smell) and self-reported taste acuity, respectively. Regression analyses will be conducted to investigate the association between loss of smell and taste acuity and self-reported appetite and food-related quality of life. All statistical analyses will be completed using SPSS (IBM Corporation).

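### The sample is called population-based but consists of volunteers presenting for hospital swabs, so the prevalence claim should be limited to that group and reported by reason for the swab

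*Protocol article*

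**What the plan says.** The Abstract's Conclusions say the study will be the first to collect longitudinal smell and taste data on infection "confirmed by PCR swab test, in a population-based cohort".

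Three other places describe who is recruited:
- Abstract, Methods: "volunteers will be recruited when they present for COVID-19 screening by respiratory tract polymerase chain reaction test".
- Study Design: "Participants will be recruited from volunteers presenting at hospitals and hospital facilities across Singapore for COVID-19 screening".
- Recruitment Procedure: "Participants will be recruited from patients applying to a hospital and its ancillary units for COVID-19 screening". People are approached after the swab.

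The first primary objective in the Introduction is to "assess the prevalence of sudden changes in smell and taste sensitivity with COVID-19 infection in a population at risk for COVID-19 infection in Singapore". The Introduction also reports that many public health bodies worldwide recommend that "individuals who experience sudden changes in sensory acuity should self-isolate and present for diagnostic testing". Statistical Analysis plans a logistic regression that also allows "comparison of smell and taste loss as a predictor of COVID-19 infection compared to other symptoms, such as fever and dry cough".

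The baseline variables in Table 1 include no reason for the swab. Data Management puts everyone with a swab result and the required Day 0 measures into the cross-sectional comparisons. Study Limitations covers compliance, retention and the suprathreshold stimuli, but not selection into testing or volunteering.

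**The concern.** A population-based cohort is drawn from a defined population regardless of the condition being measured. Here a person enters by presenting for a swab and then agreeing to a daily smell and taste study. If smell loss makes either step more likely, it is over-represented among the cases, and its prevalence is the subject of objective 1.

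The at-risk population named in that objective is wider than the people who present and volunteer. The Discussion also carries the findings over to asymptomatic and pre-symptomatic carriers, the people least likely to enter through symptom-driven testing. A second worry is the comparison of smell loss with fever and cough as predictors, if those symptoms also bring people in.

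**Working it through.** **Label against recruitment text.** The three recruitment statements differ in breadth (facilities across the country in one, a hospital and its ancillary units in another). All three describe people who present for a swab, and two call them volunteers. None describes sampling from a population, so the label does not fit.

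**Prevalence among cases.** The plan gives no design figure for prevalence, so there is none to reproduce; its sample size of 235 plays no part here. Let p be the true proportion of infected people with smell loss, and r the probability of being swabbed and enrolled with smell loss divided by that without, among the infected. Then

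observed prevalence = r·p / (r·p + 1 − p).

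The Introduction supplies two illustrative values of p: 22.6% (a Singapore cohort) and 52.7% (a pooled estimate). The documents give no value of r, so the range is assumed. Example: r = 2 and p = 0.226 gives 0.452 / (0.452 + 0.774) = 0.369.

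| Assumed r | True 22.6% | True 52.7% |
|---|---|---|
| 0.5 | 12.7% | 35.8% |
| 1 | 22.6% | 52.7% |
| 1.5 | 30.5% | 62.6% |
| 2 | 36.9% | 69.0% |
| 3 | 46.7% | 77.0% |

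**Symptom odds ratios.** The Singapore predictive values in the Introduction (24.1% positive, 96.5% negative) give a smell odds ratio of (0.241/0.759) × (0.965/0.035) = 8.75. With 22.6% taken as the sensitivity, they imply smell loss in about 3.2% of test-negatives. Assume fever in 40% of cases and 10% of controls, independent of smell loss within each group. The fever odds ratio is then (0.4/0.6)/(0.1/0.9) = 6.0.

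- *Testing depends on smell loss alone, equally in cases and controls.* The factor r cancels, and the odds ratios stay at 8.75 and 6.0.
- *Any symptom raises testing k-fold.* Each unadjusted odds ratio is multiplied by (1 − q0 + k·q0)/(1 − q1 + k·q1), where q1 and q0 are the frequencies of the other symptom in cases and controls. For smell at k = 2: 8.75 × 1.1/1.4 = 6.88.

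| Assumed k | Smell OR | Fever OR | Observed smell prevalence in cases |
|---|---|---|---|
| 1 | 8.75 | 6.00 | 22.6% |
| 2 | 6.88 | 5.05 | 29.4% |
| 3 | 5.84 | 4.40 | 32.7% |
| 5 | 4.71 | 3.56 | 36.0% |

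These are odds ratios for one symptom at a time. If testing depends only on the symptoms in a joint model and not otherwise on infection, the probability of infection given those symptoms is the same among the tested, and mutually adjusted odds ratios are not attenuated this way. Statistical Analysis does not say which form will be used.

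**Which subgroup to look at.** Restricting to everyone not swabbed for smell or taste loss removes people because they have the outcome. With no selection at all (r = 1), and half of infected participants with smell loss citing it as their reason, 22.6% becomes 0.113/0.887 = 12.7%, and 52.7% becomes 0.2635/0.7365 = 35.8%. Only swabs taken for reasons unrelated to symptoms avoid this.

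**The case against.** The label sits in a sentence about being first to collect longitudinal data. It is not attached to the prevalence objective, which is limited to an at-risk population, nor to the symptom comparison. The logistic model predicts testing positive, for which people being tested are a legitimate target group. The questionnaire in Multimedia Appendix 1 is not available here and may already record why the person was swabbed; stratification is often left to a fuller plan. All of this stands, and it limits the point to the label, the scope of objective 1 and the silence on selection.

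A reader might infer three stronger things that the documents do not support:
- *Participants came because they were told to present with smell loss.* The Introduction reports a recommendation by bodies worldwide. It does not name Singapore in that sentence or say why these participants came.
- *Prevalence is inflated.* That needs r above 1. It is the likelier direction, but no figure establishes it, and the table shows no change at 1 and a fall at 0.5.
- *The symptom comparison is distorted.* Selection on smell loss alone, the only route the document states, leaves the odds ratios unchanged. Under the any-symptom assumption both shrink and smell stays ahead: their ratio moves from 8.75/6.0 = 1.46 to 4.71/3.56 = 1.32 at a five-fold effect.

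What the objection does not remove is a stated design property that the recruitment text contradicts, next to a primary prevalence objective.

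**Conclusion.** The point holds in a limited form. The sample is not population-based on the document's own account, and the prevalence it yields describes volunteers presenting for hospital swabs. That prevalence may be overstated: with r assumed between 1.5 and 3, a true 22.6% would be seen as 30.5% to 46.7%, and a true 52.7% as 62.6% to 77.0%. Neither the size nor the direction can be settled from the documents. Unadjusted symptom odds ratios may be attenuated if several symptoms each prompt testing, which is plausible but not stated; they are unaffected if selection is on smell loss alone. The point deserves correction because it decides what objective 1 can claim, and the correction is cheap.

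**What to change.** 1. Replace the population-based label with a description of volunteers presenting for hospital swab testing, and limit the objective 1 prevalence claim to that group.
2. Unless the Singapore Smell and Taste Questionnaire already captures it, add one Day 0 question on the reason for the swab: smell or taste loss, other symptoms, contact, or routine or mandatory screening. Ask the participant, because the record access described under Exclusion Criteria and COVID-19 Diagnosis covers only the swab result.
3. Report prevalence and the logistic odds ratios overall and by reason. Use those swabbed for reasons unrelated to symptoms (contact or routine screening) as the sensitivity estimate least affected by symptom-driven testing. It does not remove selection through volunteering. Do not use everyone not swabbed for smell or taste loss, which would bias prevalence downward.
4. Add selection into testing and volunteering to Study Limitations.

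Cost: one question, one stratified table and a minor amendment reported to the review board. Strata will be small and the claim narrower. Participants already enrolled (69 by October 2, 2020) would have no recorded reason; at that date 235 − 69 = 166 of the minimum sample were still to be recruited.

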**Trial Registration:**

ClinicalTrials.gov NCT04492904; https://clinicaltrials.gov/ct2/show/NCT04492904.

**International Registered Report Identifier (IRRID):**

DERR1-10.2196/24797

## Introduction

Early identification of symptoms associated with SARS-CoV-2, which causes COVID-19, has been recommended to encourage early diagnostic testing and self-isolation and to reduce the risk of community spread of infection. High temperature, continuous dry cough, and fatigue are common clinical symptoms associated with COVID-19 infection; however, numerous recent reports from patients and clinicians worldwide have consistently identified a sudden loss of smell (anosmia) and/or taste (ageusia) as a key early symptom of infection [1-6].

Recent self-report questionnaire data from many countries highlights an association between sudden onset smell and taste loss and COVID-19 infection, with reported incidences of changes in sensory acuity ranging from 11% to >60% [7-13]. A recent systematic review and meta-analysis of studies investigating loss of smell and/or taste with COVID-19 infection reported a pooled prevalence of 52.7% and 43.9% for olfactory and gustatory dysfunction, respectively [14]. Also, Hopkins et al [15] found that 1 in 6 patients reported new onset anosmia as an isolated symptom. The onset of smell and/or taste loss is often abrupt and, unlike other upper respiratory tract infections, it often occurs in the absence of nasal obstruction [13,16]. Importantly, the loss of smell and/or taste occurs early during COVID-19 infection, often before the onset of more established symptoms [8,17-20], and this loss may be an important marker of infection. This finding has prompted many global public health bodies to recommend that individuals who experience sudden changes in sensory acuity should self-isolate and present for diagnostic testing [2-4,21-24].

The majority of published studies investigating smell and taste loss related to COVID-19 have used subjective measurements of smell and taste, specifically self-report questionnaires. In Singapore, there have been anecdotal reports of smell and taste loss with COVID-19 infection [25,26], and in one prospective cohort of patients with COVID-19, it was found that 22.6% experienced acute olfactory loss [27]. The positive predictive value of acute olfactory loss for COVID-19 was 24.1%, and the negative predictive value was 96.5% [27]. Data collected to date have been based largely on self-report questionnaire measures, and there is a lack of objective data on measured smell and taste sensitivity. One study used a validated smell test, the University of Pennsylvania Smell Identification Test (UPSIT), to compare smell acuity in patients diagnosed with COVID-19 with a matched control group; it was shown that 98% of the patient group exhibited some smell dysfunction, scoring significantly lower on the UPSIT compared to controls [28].

In addition, to our knowledge, no longitudinal study has yet been performed to systematically track the onset, severity, and recovery of changes to sensory acuity across the preinfection and postinfection periods of COVID-19, with emerging reports of sustained anosmia among a small proportion of people who have recovered from infection. To date, questionnaire measures alone have been published; these studies relied on self-reporting and may not accurately reflect the true extent of smell and taste changes during COVID-19 infection in the absence of a standardized tool for such measurements. Reliance on self-report questionnaire data and variable approaches could help explain the wide variability in the reported prevalence of olfactory dysfunction with COVID-19 infection (5%-98%) [29]. Therefore, there is a need for objective testing of smell and taste loss in patients infected with COVID-19 using standardized smell and taste stimuli [29-31]. Moreover, due to extensive restrictions on movement, the need to socially distance, and the potential for infection spread with reusable standardized odor and taste test materials, the collection of in-person physical data is challenging. Furthermore, although clinically validated smell and taste assessments are preferred, they are often expensive, and their reuse is not recommended among infected patient populations. Home use sensory tests have been developed to track changes in smell and taste sensitivity using common household items as test stimuli [32,33]. However, these tests rely on participants sourcing and preparing their own test stimuli from available household items; this introduces unwanted stimulus variation, which may present problems for comparability of smell loss across individuals using different stimuli.

The COVOSMIA-19 study will standardize the smell and taste stimuli used by all participants to ensure consistency and provide a disposable, rapid, self-administered home use test, the Singapore Smell and Taste Test (SSTT), to minimize the risk of cross-contamination and infection spread. The trial will enable self-testing for up to 28 consecutive days and will provide a standardized longitudinal assessment of smell and taste function to enable tracking of the onset, severity, and recovery of the sensory changes reported to occur with COVID-19 infection. The standardized smell and taste test will also be compared with self-reported questionnaire measures of smell and taste changes and measured changes to sensory acuity using common household items (an approach previously used by [32]).

The primary objectives of this study are to (1) assess the prevalence of sudden changes in smell and taste sensitivity with COVID-19 infection in a population at risk for COVID-19 infection in Singapore, (2) establish the temporal onset, severity, and recovery of changes in smell and taste sensitivity with COVID-19 infection, and (3) evaluate the efficacy of the SSTT as a rapid, cost-effective, self-administered measure of changes to smell and taste compared to previous measures using household items. The secondary objective of this study is to investigate the effects of loss of smell and taste acuity on food enjoyment and appetite as well as to establish the impact of COVID-19 infection on food-related markers of quality of life. We hypothesize that loss of smell and taste acuity will be associated with COVID-19 infection, will return upon recovery from infection for the majority of patients, and will result in short-term reductions in appetite, food enjoyment, and food-related quality of life.

